14.2. Safety analysis set

(1) Adverse events

Subjects who experienced an adverse event and consumed the trial product at least once

(2) Examination values

Subjects who completed all of the trial’s designated schedule and content

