4.1. Type and name of trial product

(1) Trial product: Food product containing enzyme-treated royal jelly (RJ)

(2) Placebo: Food product with no RJ

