**15. Evaluation methods**

15.1 Evaluating efficacy

(1) Primary outcomes: subjective dry eye symptoms, BUT, keratoconjunctival disorders, Schirmer’s test

(2) Secondary outcomes: functional vision

(3) Efficacy evaluation methods

For each item, values before consumption and at each time point after consumption will be compared between the trial group and the placebo group using a 2-sample t-test. The amount of change from before consumption to each time point after consumption will be compared between the trial group and the placebo group using a 2-sample t-test. Values at each time point after consumption will be compared to values before consumption in each group using a 1-sample t-test.

For the baseline characteristics of patients with dry eye, Student’s t-test (p ≥ 0.05 by the F-test) will be used for comparison of age, and Pearson chi-square test will be used for categorical data of gender and dry eye diagnosis. Repeated measures analysis of variance followed by Tukey's honest significant difference (HSD) post hoc test will be used for analysis of dry eye symptoms. For the biochemical analysis, paired t-tests will be used for within-group comparisons and the F-test, followed by Student’s t-test (p≥0.05 by the F-test) will be used for between-group comparisons (placebo vs. RJ). A p-value of <0.05 was considered statistically significant. 16.2. Evaluating safety

(1) Outcomes

These are adverse events confirmed from interviews and journal entries (subjective symptoms), and abnormal variations in body weight and scientific examination values. For examination values, changes in items will be checked: body weight, systolic blood pressure, diastolic blood pressure, heart rate, and biochemical data.

(2) Evaluation methods

The number of adverse events and abnormal variations will be totaled to create a table. If the same adverse event occurs in the same subject multiple times, it will be treated as one event. To evaluate changes in examination values, measurements before consumption and at each time point after consumption will be compared using a 1-sample t-test. Figures will be displayed as mean ± standard deviation (or standard error). The significance level will be 2-sided 5%.

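### Section 14.2 limits the adverse-event set to subjects who had an event and the examination-value set to full completers, so neither describes safety in everyone exposed

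*Protocol*

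**What the plan says.** Protocol section 14.2 sets out two safety populations. For adverse events it is "Subjects who experienced an adverse event and consumed the trial product at least once". For examination values it is "Subjects who completed all of the trial’s designated schedule and content". No other section defines a population of all exposed subjects.

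The safety evaluation (headed 16.2, following 15.1) states how these sets are used:
- Adverse events: "The number of adverse events and abnormal variations will be totaled to create a table". A repeat rule adds: "If the same adverse event occurs in the same subject multiple times, it will be treated as one event".
- Examination values: the items are "body weight, systolic blood pressure, diastolic blood pressure, heart rate, and biochemical data", and "measurements before consumption and at each time point after consumption will be compared using a 1-sample t-test".

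No percentage, incidence or between-group test is stated for adverse events.

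**The concern.** A safety population should hold everyone at risk of an event, so that the number affected can be set against the number exposed. The adverse-event definition joins two conditions with 'and', and one of them is the outcome itself. A subject who took capsules for 8 weeks without any event does not belong to the set.

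The second definition has a different weakness. Section 13.2 lets the investigator withdraw a subject whose safety could be at risk. That subject does not complete the schedule, and so leaves the before-and-after analysis of weight, blood pressure, heart rate and biochemistry. Membership can therefore depend on the safety outcome under study. The condition also covers all the trial's content, so missing one eye test removes a subject's blood pressure and laboratory values too.

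At stake is whether the trial can describe the risk in those exposed and set it beside placebo on a proper base.

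**Working it through.** The protocol gives no incidence, dropout rate or safety target, so there is no stated figure to reproduce. The checks below use direct proportions and a comparison of sections.

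**Inputs.** 25 subjects per arm at the start of consumption (6.1). Set definitions from 14.2. Visit schedule from the examination table placed before section 10. Event counts and dropout rates are assumptions, because the protocol states none.

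**1. Adverse-event set.** Let k be the number of subjects in an arm with at least one event among those who consumed.

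- Incidence in the set as written: k/k = 100% for every k ≥ 1, and 0/0 (undefined) for k = 0.
- Incidence among all exposed: k/25.

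| k (assumed) | Set as written | All exposed |
| --- | --- | --- |
| 1 | 1/1 = 100% | 1/25 = 4% |
| 2 | 2/2 = 100% | 2/25 = 8% |
| 5 | 5/5 = 100% | 5/25 = 20% |
| 8 | 8/8 = 100% | 8/25 = 32% |
| 10 | 10/10 = 100% | 10/25 = 40% |

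With 2 affected subjects in one arm and 8 in the other, the set as written gives 100% against 100%. The exposed population gives 8% against 32%, a difference of 24 percentage points.

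**2. Examination-value set.** The schedule table shows which values exist when a subject stops early:

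| Item | Pre-consumption | Week 4 | Week 8 |
| --- | --- | --- | --- |
| Weight, blood pressure, heart rate | yes | yes | yes |
| Biochemistry | yes | no | yes |

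- A subject who attends week 4 and then stops has a usable pair (before, week 4) for weight, blood pressure and heart rate. The safety section plans a test at each time point, so that pair has a place in the analysis. The completer rule discards it.
- The same subject has no scheduled biochemistry after baseline, so the rule discards no scheduled laboratory pair.
- A subject who stops before week 4 has no scheduled later value of any kind.
- A subject who attends every visit but misses one unrelated examination loses all safety values, biochemistry included.

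**3. Size of the completer restriction.** One excluded subject is 1/25 = 4% of an arm. If dropout across the 50 subjects were 5%, 10% or 20% (assumed), the rule would remove 50 × 0.05 = 2.5, 50 × 0.10 = 5 or 50 × 0.20 = 10 subjects. Only those who stop after week 4 would have scheduled values to recover.

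**The case against.** **Only counts are planned.** This stands as far as it goes. The protocol does not state that a percentage will be calculated, and a count of events per arm is the same whether or not event-free subjects belong to the set. A reader might infer that the trial will report 100% incidence; the protocol does not say so. That figure is only what the named set implies as a denominator.

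**Rates can still be formed.** A reader might infer that adverse-event rates cannot be calculated at all. That is too strong, since 25 per arm is stated in 6.1 and events are recorded on case report forms (12.3). But this means going outside the defined set. It also needs the number of subjects affected, which a total of events need not equal: one subject with two different events adds two.

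**Placebo subjects.** Section 4.1 uses 'trial product' for the royal jelly food and lists placebo separately, so a reader might infer that placebo subjects are dropped. The rest of the protocol does not support this. Sections 10.1, 10.4, 12.1 and 14.1 use the term for whatever a subject was allotted. On the narrow reading, placebo subjects could not have an adverse event under 12.1 and would fail the 80% intake rule in 14.1, leaving no placebo group to compare.

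**Laboratory values.** A reader might infer that the completer rule hides the biochemistry of early stoppers. Biochemistry is scheduled only before consumption and at week 8, so for those subjects no scheduled later values exist to be removed.

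**Abnormal values can be recorded as adverse events.** Sections 12.1 and 12.2 allow this, and abnormal variations are tabulated, so a non-completer's abnormal value need not vanish. This helps in part only: the measurements still leave the before-and-after tests.

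**Loose wording.** The sentence may have been meant to cover everyone who consumed the product, but nothing in the protocol says so.

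**Conclusion.** Both definitions need correcting. The adverse-event set conditions on the outcome and supplies no valid denominator; this follows from the wording and needs no assumption. The percentages in the working rest on assumed event counts and on all 25 subjects per arm starting consumption.

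The completer rule discards week-4 weight, blood pressure and heart rate of subjects who stop later, some possibly for safety, and all safety values of a subject who misses any unrelated examination. A reader might infer that the summaries are shown to be biased towards safety. That direction is plausible, but with no dropout rate or pattern of reasons in the protocol it can be neither established nor sized.

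No sample size, significance level or efficacy result depends on this point.

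**What to change.** Reword 14.2 as follows.

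1. **Adverse events:** all subjects who consumed at least one capsule of the royal jelly product or placebo, grouped by product taken. Naming both products also removes the ambiguity left by 4.1. Alongside the planned event counts, report subjects with at least one event as n/N per group.
2. **Examination values:** every such subject with a pre-consumption value and at least one later value that was obtained, item by item. No early-termination visit is required, since the schedule has none. Values from the repeat or follow-up examinations allowed in 10.2 and 12.5 can be used where they exist.

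Make the change before the analysis set is fixed, because 6.2 opens the allocation table only after that step.

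The cost is a protocol amendment with ethics re-approval (16.3) and slightly different numbers of subjects by time point. No new data collection is needed. For early stoppers biochemistry gains little, because its only scheduled later value is at week 8.

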**15. Evaluation methods**

15.1 Evaluating efficacy

(1) Primary outcomes: subjective dry eye symptoms, BUT, keratoconjunctival disorders, Schirmer’s test

(2) Secondary outcomes: functional vision

(3) Efficacy evaluation methods

For each item, values before consumption and at each time point after consumption will be compared between the trial group and the placebo group using a 2-sample t-test. The amount of change from before consumption to each time point after consumption will be compared between the trial group and the placebo group using a 2-sample t-test. Values at each time point after consumption will be compared to values before consumption in each group using a 1-sample t-test.

For the baseline characteristics of patients with dry eye, Student’s t-test (p ≥ 0.05 by the F-test) will be used for comparison of age, and Pearson chi-square test will be used for categorical data of gender and dry eye diagnosis. Repeated measures analysis of variance followed by Tukey's honest significant difference (HSD) post hoc test will be used for analysis of dry eye symptoms. For the biochemical analysis, paired t-tests will be used for within-group comparisons and the F-test, followed by Student’s t-test (p≥0.05 by the F-test) will be used for between-group comparisons (placebo vs. RJ). A p-value of <0.05 was considered statistically significant. 16.2. Evaluating safety

(1) Outcomes

These are adverse events confirmed from interviews and journal entries (subjective symptoms), and abnormal variations in body weight and scientific examination values. For examination values, changes in items will be checked: body weight, systolic blood pressure, diastolic blood pressure, heart rate, and biochemical data.

(2) Evaluation methods

The number of adverse events and abnormal variations will be totaled to create a table. If the same adverse event occurs in the same subject multiple times, it will be treated as one event. To evaluate changes in examination values, measurements before consumption and at each time point after consumption will be compared using a 1-sample t-test. Figures will be displayed as mean ± standard deviation (or standard error). The significance level will be 2-sided 5%.

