**2. Trial objective**

The objective is to evaluate the effects of 8 continuous weeks of consumption of a food product containing royal jelly on the subjective assessment of dry eyes as well as ophthalmological examination results, in men and women aged between 20 and 60 years with dry eye symptoms, and to compare these effects to those of a placebo.

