**10. Schedule and examination content**

10.1. Trial schedule

(1) Preliminary examinations will be performed on candidate subjects who give consent. These will include a lifestyle questionnaire, interview, physical measurements, scientific measurements, ophthalmological examinations ( fundoscopy, vision test, refractometry, Schirmer’s test), and subjective evaluation of dry eyes (questionnaire).

(2) Fifty people who fit the objective of the trial will be selected based on the results of the preliminary examinations.

(3) The subjects who are selected will come to the clinic for pre-consumption examinations, which will include an interview, physical measurements, scientific measurements, ophthalmological examinations (functional vision test, break-up time of tear film (BUT), keratoconjunctival disorders), and subjective evaluation of dry eyes (questionnaire).

(4) After the pre-consumption examinations, the subjects will be given the allotted trial product so that they can begin taking it the following day. They will also begin making journal entries of details such as the time they consume the trial product.

(5) The subjects will come to the clinic during the fourth and eighth weeks of the trial to undergo physical measurements, scientific measurements, and ophthalmological examinations (functional vision test, BUT, keratoconjunctival disorders, Schirmer’s test).

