10.3. Survey and examination content

See the schedule above.

| Item | Content | |
| --- | --- | --- |
| Lifestyle questionnaire | Medical history, medical product and health food intake, allergies, smoking status, alcohol intake, subjective dry eye symptoms (DEQS), etc. | |
| Interview | Inquire about physical condition, check for adverse events | |
| Physical measurements | Height*^1^, weight, BMI | |
| Scientific examinations | Systolic blood pressure, diastolic blood pressure, heart rate, biochemical data(total protein, aspartate aminotransferase, alanine transaminase, lactate dehydrogenase, alkaline phosphatase, gamma-glutamyl transferase, urea nitrogen, creatine, uric acid, total cholesterol, low-density lipoprotein cholesterol, high-density lipoprotein cholesterol triglyceride, glucose, haemoglobin A1c) | |
|  | Fundoscopy | Examination by physician during interview*^1^ |
|  | Vision test | Measured using a visual examination device*^1^ |
|  | Functional vision test, | Examined using a functional optometer*^2^ |
|  | Refractometry | Examined using autorefractor keratometer*1 |
|  | BUT | Fluorescein BUT*^2^ |
|  | Keratoconjunctival disorder | Fluorescein stain test*^2^ |
|  | Schirmer’s test | *^3^ |

1. ^1^: Performed at preliminary examination only
2. ^2^: Performed starting with pre-consumption examination
3. ^3^: Performed at preliminary examination and eighth-week examination

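### Four co-equal primary outcomes are each tested several ways at an unadjusted 5%: an inert product has about a 43-51% chance of some significant primary difference, and about 23-29% of one favouring royal jelly

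*Protocol*

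**What the plan says.** Protocol 15.1 (1) reads: "Primary outcomes: subjective dry eye symptoms, BUT, keratoconjunctival disorders, Schirmer’s test". It gives no order among the four.

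Protocol 15.1 (3) then prescribes three sets of tests for every item:

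- Between groups, raw values: "For each item, values before consumption and at each time point after consumption will be compared between the trial group and the placebo group", by a 2-sample t-test.
- Between groups, changes: "The amount of change from before consumption to each time point after consumption will be compared between the trial group and the placebo group", also by a 2-sample t-test.
- Within each group: "Values at each time point after consumption will be compared to values before consumption in each group using a 1-sample t-test".

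For dry eye symptoms alone, the same section adds a repeated-measures analysis of variance with Tukey's HSD. The decision rule is "A p-value of <0.05 was considered statistically significant".

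On timing, Protocol 10.1 says "The subjects will come to the clinic during the fourth and eighth weeks of the trial", so there are two post-consumption time points. The objective in Protocol 2 is to "evaluate the effects of 8 continuous weeks of consumption", but 15.1 does not make Week 8 the deciding visit. For Schirmer's test the documents disagree. The schedule table and 10.1 (5) include it at Weeks 4 and 8, while a footnote in 10.3 says "Performed at preliminary examination and eighth-week examination".

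**The concern.** A primary analysis should tell the reader in advance which result decides the trial. Here up to sixteen placebo-controlled comparisons carry primary status, all at the same threshold. The protocol does not leave this open for a later document: it names the tests and the threshold for each. If the product does nothing, the plan as written still offers many routes to a significant primary result, and the one to emphasise could be picked once the allocation is known. A single p-value below 0.05 among them would then be much weaker evidence than it appears.

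**Working it through.** The protocol states no family-wise error rate, power or sample-size derivation, so there is no figure of its own to reproduce.

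**Inputs from the protocol.** Four primary outcomes, two scales (value and change) and p<0.05 per test (15.1); two post-consumption visits (10.1 and the schedule table); 25 per group (6.1).

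**Inputs assumed, because the documents give none.** Correlation of 0 to 0.5 between outcomes and 0.5 to 0.7 between visits; normally distributed data; all 25 per group analysed; no effect on any outcome.

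**Count of between-group tests after baseline.** 4 outcomes x 2 visits x 2 scales = 16. If Schirmer's test has no Week-4 measurement, its two Week-4 tests drop out, leaving 14.

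**Upper reference, if the tests were independent.**

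- Either direction: 1 - 0.95^16 = 0.560; 1 - 0.95^14 = 0.512.
- Favouring royal jelly (2.5% per test): 1 - 0.975^16 = 0.333; 1 - 0.975^14 = 0.298.

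**Allowing for dependence.** The tests are correlated, so the true figures are lower. I simulated 20,000 trials per setting: 25 per arm, four outcomes at three visits, pooled two-sample t-tests on values and on changes at both later visits. Each range below spans visit correlations 0.5, 0.6 and 0.7.

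| Correlation between outcomes | 16 tests, either direction | 16 tests, favouring royal jelly | 14 tests, either direction | 14 tests, favouring royal jelly |
| --- | --- | --- | --- | --- |
| 0 | 50.2-51.1% | 29.0-29.3% | 46.4-47.3% | 25.9-26.9% |
| 0.2 | 49.1-50.1% | 26.7-27.7% | 45.6-45.8% | 24.7-25.1% |
| 0.3 | 47.6-47.9% | 25.7-26.7% | 43.6-44.1% | 23.2-23.9% |
| 0.5 | 43.4-43.9% | 23.2-23.7% | 40.4-41.3% | 21.5-22.0% |

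Widening the visit correlation to 0.3-0.8 lowers the bottom of each overall range by at most 0.5 points (to 43.0%, 22.7%, 40.0% and 21.2%) and leaves the top unchanged.

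**Where the inflation comes from.**

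- Change scores only, both visits (8 tests): about 26-32% in either direction and 13-17% favourable.
- Week-8 change only (4 tests), if independent: 1 - 0.95^4 = 0.185 in either direction and 1 - 0.975^4 = 0.096 favourable. So choosing the visit and the scale helps, but does not remove the problem across outcomes.
- The within-group tests are not in these counts. Adding those in the royal jelly arm raises the either-direction figure for 16 tests to about 54-62%, even with no change over time.

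**After the fix.** Four independent tests at 0.05/4 = 0.0125 give 1 - 0.9875^4 = 0.049.

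**Power cost at 25 per group, 80% power.** The normal approximation is d = (z for alpha/2 + z for power) x sqrt(2/25).

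- Alpha 0.05: (1.960 + 0.842) x 0.283 = 0.79, or 0.81 SD with the t distribution.
- Alpha 0.0125: (2.498 + 0.842) x 0.283 = 0.94, or 0.98 SD with the t distribution.

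**The case against.** - **Either direction is not benefit.** A reader might infer that 43-51% is the chance of a false claim of benefit. It is not. The 5% level is taken as two-sided, so that figure includes differences favouring placebo. The chance of a result favouring the product is about 23-29%, roughly half. This objection stands, and the two figures must be kept apart.
- **Sixteen is not a settled count.** The 10.3 footnote supports 14. That also stands; the defect remains on either count.
- **Some adjustment is present.** Tukey's HSD adjusts among comparisons within dry eye symptoms. It does nothing across the four outcomes, and the per-item t-tests still apply to symptoms. The effect is to give that outcome two competing analyses.
- **No family-wise rate is promised.** A reader might infer that the plan breaks a stated overall 5%. The efficacy text gives only a per-test threshold, and the two-sided 5% sentence sits in the safety text. Nor does any rule say that one significant test makes the trial positive. The figures therefore measure the opportunity for a false-positive primary result, not a broken commitment.
- **The SAP may settle it.** Multiplicity rules are often placed there, and the objective already points to eight weeks. But a SAP that picked one contrast and adjusted across outcomes would have to override tests that 15.1 gives equal standing. The point rests on what 15.1 fixes, not on what it omits.

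**Conclusion.** The point holds. Protocol 15.1 gives four outcomes equal primary status and tests each on two scales at each visit, all at 5%, with no deciding contrast and no control across outcomes. Under the assumed correlations and 25 analysed per group, an inert product yields at least one significant primary difference in about 43-51% of trials. In about 23-29% of trials at least one favours royal jelly. The benchmarks for a single two-sided 5% test are 5% and 2.5%, so the favourable figure is about nine to twelve times its benchmark (23/2.5 = 9.2; 29/2.5 = 11.6). With Schirmer's test at Week 8 only, the figures are about 40-47% and 21-27%. The exact values depend on correlations that the documents do not give, but at every setting tried the inflation is several-fold.

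**What to change.** In Protocol 15.1:

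1. For each of the four outcomes, make the between-group difference in change from pre-consumption to Week 8 the single primary contrast, with one named analysis. For dry eye symptoms, state that this contrast is primary and that the repeated-measures analysis with Tukey's HSD is supportive.
2. Hold the four outcomes at an overall two-sided 5%, either by Holm or by a fixed order set in advance, each step at 5%.
3. Label the Week-4, raw-value and within-group tests supportive.
4. Reconcile the schedule table, 10.1 and the 10.3 footnote on when Schirmer's test is done. This includes which visit supplies its baseline: the table marks a pre-consumption measurement, but 10.1 (3) and the footnote do not.

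**Cost.** This is wording only, although Protocol 16.3 requires ethics re-approval of a change to an approved protocol. Under Holm the smallest p-value must be below 0.0125, which raises the detectable effect from about 0.81 to 0.98 SD at 25 analysed per group. Both values rise further if the exclusions in 14.1 reduce the numbers analysed. A fixed order spares the first outcome this loss, but once one outcome misses 5%, no later outcome can be claimed.

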**6. Number of subjects, allotment method**

6.1. Number of subjects

There will be 50 subjects when consumption is started—25 subjects taking the trial product and 25 subjects taking the placebo.

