6.2. Allotment method

The person in charge of allotment will use random numbers to create an allocation table and assign the trial product an allocation number. The person in charge of allotment will then seal the allocation table and keep it sealed until the time comes to open it. After the analysis set and data are fixed, the person in charge of allotment will unseal the allocation table and disclose the information., In the event of a serious adverse event or emergency, the allocation table can be unsealed only to disclose the minimum amount of information required.

7. Inclusion and exclusion criteria for the subjects

People who meet the following inclusion criteria and do not fall under the exclusion criteria will be selected as the subjects.

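### Baseline is significance-tested between randomised arms, while the week 4 and week 8 comparisons are left unadjusted for the baseline value

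*Protocol*

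**What the plan says.** Section 15.1(3), under the efficacy evaluation methods, states, item by item, that "values before consumption and at each time point after consumption will be compared between the trial group and the placebo group"; the method named is a two-sample t-test. Pre-consumption values thus receive the same between-arm test as the efficacy result, in the same sentence. The changes from baseline to each time point are then compared between arms by a second two-sample t-test.

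The next paragraph adds a t-test that "will be used for comparison of age", and states that a "Pearson chi-square test will be used for categorical data of gender and dry eye diagnosis". The threshold there is given as "A p-value of <0.05 was considered statistically significant". A two-sided 5% level is stated only at the end of the safety methods (16.2).

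Section 6.1 plans "25 subjects taking the trial product and 25 subjects taking the placebo", and section 6.2 makes allocation random: "The person in charge of allotment will use random numbers to create an allocation table". Section 14.1 limits the efficacy set to subjects who complete the schedule, after exclusions for low intake, missing journal entries, breaches of the restrictions and other reasons.

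None of the between-arm methods listed in 15.1(3) takes the pre-consumption value as a covariate. The repeated measures ANOVA with Tukey comparisons, named for symptoms, is not described as doing so either. Nothing in the protocol says what follows from a significant or a non-significant baseline test.

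**The concern.** In a randomised trial a between-arm test at baseline asks whether chance produced a gap, which is not what the reader needs to know. What matters is how far the observed gap moves the week 4 and week 8 comparisons. A p-value does not measure that, and a gap too small to be significant can still matter when baseline and follow-up are correlated.

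The two planned post-consumption tests respond to a baseline gap in opposite directions. The raw-value test carries part of the gap forward as if it were an effect. The change test over-corrects by subtracting the whole gap when only part of it persists. In a trial of 50 subjects, gaps of this size are ordinary. If one occurs, the sponsor would hold two between-arm results per item and time point, both distorted and possibly pointing different ways, and no adjusted one to settle the matter.

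**Working it through.** **Inputs from the protocol.** 25 per arm (6.1); threshold 5% (15.1(3)), taken as two-sided as in 16.2. Baseline tests: four primary items, one secondary item, age, gender and dry eye diagnosis, so at least 4 + 1 + 3 = 8. The protocol gives no effect size, SD or power, so there is no stated figure to reproduce, and gaps are expressed in SD units. **Assumptions:** normal outcomes, equal SD at each time point, and baseline to follow-up correlation r between 0.5 and 0.8 (not given in the protocol).

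**1. False flags at baseline.** If the tests are independent, P(at least one) = 1 − 0.95^8 = 0.337. For the five outcome items alone it is 1 − 0.95^5 = 0.226. The expected number is 8 × 0.05 = 0.4. Positive correlation between items lowers the first two figures.

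**2. Size of gap needed for a flag.** Smallest significant observed gap = t(0.975, 48) × √(2/25) = 2.011 × 0.283 = 0.57 SD. With an assumed 20 per arm left in the efficacy set it is 0.64 SD. For gender, 10/25 against 16/25 is not significant (Pearson p = 0.09).

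**3. Effect of an unflagged gap.** Take an observed baseline gap g = 0.5 SD, which is not significant at 25 per arm, and no treatment effect. Given g, the difference in follow-up means is centred at r·g and the difference in mean change at (r − 1)·g. Both have standard error √[(2/25)(1 − r²)].
- r = 0.5, raw: shift 0.25, SE √(0.08 × 0.75) = 0.245, critical value 1.96 × √0.08 = 0.554. (0.554 − 0.25)/0.245 = 1.24, so the error is about 10.8%. The change test is shifted by −0.25 with the same error.
- r = 0.7, raw: shift 0.35, SE √(0.08 × 0.51) = 0.202. (0.554 − 0.35)/0.202 = 1.01, error about 15.6%. Change: shift −0.15, critical value 1.96 × √(0.08 × 0.6) = 0.429, error about 8.5%.

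**4. Type I error given a significant baseline test.** Simulation of 200,000 null trials per correlation, 25 per arm:

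| r | Raw value | Change | Baseline-adjusted |
|---|---|---|---|
| 0.5 | 18% | 18% | 5.4% |
| 0.6 | 25% | 16% | 5.0% |
| 0.7 | 33% | 13% | 5.0% |
| 0.8 | 43% | 10% | 4.9% |

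The Monte Carlo error is about half a percentage point or less for the raw and change columns and about 0.2 points for the adjusted column.

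**5. Overall error.** Only about 5% of null trials fall in that branch. In the other 95% the raw test runs at 4.3% (r = 0.5) to 3.0% (r = 0.8). Averaging for the raw test: 0.05 × 0.182 + 0.95 × 0.043 = 0.050 at r = 0.5, and 0.05 × 0.431 + 0.95 × 0.030 = 0.050 at r = 0.8. The planned tests therefore keep their nominal level over all randomisations.

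**6. Precision.** Relative to the raw-value test, the variance of the between-arm estimate is 2(1 − r) for change and 1 − r² for the adjusted comparison, ignoring the one degree of freedom spent on the slope. At r = 0.5 this gives 1, 1.00 and 0.75; at r = 0.8 it gives 1, 0.40 and 0.36. The adjusted comparison is the most precise throughout.

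**The case against.** The strongest reply is that the baseline tests decide nothing. The protocol ties no action to a baseline p-value, plans both the raw and the change comparison whatever the result, and already brings in the baseline through the change score. This stands, and it limits the point in three ways.

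- A reader might infer that the baseline p-value will choose between the two outcome tests. No such rule is written. Even if it were followed (change when the baseline test is significant, raw otherwise), the overall error would be 0.05 × 0.177 + 0.95 × 0.043 = 5.0% at r = 0.5 and 0.05 × 0.099 + 0.95 × 0.030 = about 3.3% at r = 0.8.
- A reader might infer that non-significant gaps will be passed off as comparable. The protocol does not say so.
- A reader might say that the null hypothesis at baseline is true by design, so that every significant result is chance. That holds for all randomised subjects. In the completer set of section 14.1, a gap may also reflect exclusions made after randomisation. A p-value at this sample size is still a poor check for that.

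It is also tempting to object that dry eye diagnosis is undefined. That is a missing detail which an analysis plan could supply, and it is not part of this point.

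The change score does not answer the rest. It trades one distortion for the opposite one, as steps 3 and 4 show.

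**Conclusion.** The point holds in a limited form. The baseline tests are uninformative: about 34% chance of at least one false flag if the eight tests are independent, and no flag below an observed gap of 0.57 SD. They do not by themselves inflate the type I error at week 4 or week 8.

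The substantive weakness is that both planned between-arm t-tests are unadjusted. When a significant baseline gap occurs, the error is about 18% to 43% for raw values and 18% to 10% for change as r goes from 0.5 to 0.8. A gap of 0.5 SD that goes unflagged already gives about 9% to 16% at r = 0.5 to 0.7. A baseline-adjusted comparison stays near 5% in either case and is more precise.

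The conditional figures rest on assumed correlations, normality and the full 25 per arm, and they describe the unlucky trial, not the average one. This is an improvement available at almost no cost, not a correction of an invalid test.

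**What to change.** In section 15.1(3), replace the between-arm t-tests of raw values and of change at weeks 4 and 8 with one comparison per item and time point, adjusted for that item's pre-consumption value (ANCOVA or an equivalent model). State that the adjustment applies whatever imbalance is observed. Delete the between-arm tests of pre-consumption values, age, gender and dry eye diagnosis, and describe baseline by arm with mean and SD, or counts, without p-values.

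Name the covariate for Schirmer's test explicitly. The visit schedule marks a pre-consumption measurement, but section 10.1(3) does not list one and the footnote in 10.3 limits the test to the preliminary and eighth-week visits. These places must be reconciled; a preliminary value appears in all of them.

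The cost is a text amendment, with the ethics re-approval that section 16.3 requires, one degree of freedom per comparison, and the usual check that a linear baseline slope is reasonable for scored items. No further subjects, visits or measurements are needed. The amendment should be made before the allocation table is unsealed.
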